## **12.4 Audits and Inspections**

Inspections by regulatory authorities during the study or after the study is completed are performed to ensure proper study conduct and data handling procedures according to ICH-GCP guidelines and regulatory requirements. Inspections may include verification of all source documents, e-CRF, site files, and a visual inspection of the study site. Direct access to all documents and sites involved in the study will be provided by the study staff members. In case of an announced inspection immediate notification of the other party is necessary.

## **12.5 Confidentiality, Data Protection**

Direct access to source documents will be permitted for purposes of monitoring (12.3). The participants name or other personal identifiable data are not recorded in the CRF as well as eCRF. Subjects' confidentiality will be ensured by utilising unique identification numbers to correspond the data. Each participant will be coded by a number during the screening. After electronic enrolment to the study, the participant will be assigned with a unique personal study number (patient ID). All data collected for the study will be entered under the patient ID only.

The relation between the patient ID and participant's name, address, date of birth and screening number will be documented in a written register ("patient identification list"). The patient identification list will be stored in the research study office of the department of Neurosurgery, University Hospital of Basel.

The Sponsor, PI, Co-Investigator and study nurses will have access to the protocol and dataset. While the CEB statistician will have access to the statistical codes during and after the study.

Study data entered into the EDC system is only accessible by authorized persons. Once the data of all subjects is transferred to the EDC system, the database will be locked and closed for further data entry. The complete study dataset is exported, encrypted and transferred to the principal investigator through a secured channel by the responsible Data Manager at University Hospital Basel.

## **12.6 Storage of biological material and related health data**

After completion of the study the data and materials will be stored at REDCap data capture program which is accessible via a standard browser on a www-connected device. Password protection and user-right management will still apply and ensures that only authorized persons can enter the EDC system to view data and use it for further research according to their permissions.

Exported data will be archived by the principal investigator in a locked cupboard within the offices of the Neurosurgical Department of the University Hospital of Basel.

### **13 PUBLICATION AND DISSEMINATION POLICY**

- The trial is registered at [clinicaltrials.gov](https://clinicaltrials.gov) and at [www.kofam.ch](http://www.kofam.ch).
- The study protocol is submitted as publication in a peer reviewed medical journal for trial protocols (Trials).
- Publication of the final study results will be published in a top tier peer reviewed medical journal.

## **14 FUNDING AND SUPPORT**

### **14.1 Funding**

The study will be financially supported by the research foundation of the department of Neurosurgery of the University Hospital of Basel and we applied for further funding at different other foundations.

### **14.2 Other Support**

**N/A**

## **15 INSURANCE**

Insurance will be covered by the business liability insurance of the Department Neurosurgery, University Hospital of Basel.

## APPENDICES

1. Medical Devices:
  - a. US burr hole probe:
    - <https://www.bkmedical.com/transducers/n11c5s-burr-hole/>
  - b. Brainlab Dual Curve System (cranial navigation software version 3.1.):
    - <https://www.brainlab.com/de/chirurgie-produkte/uebersicht-ueber-neurochirurgie-produkte/kraniale-navigation/>
2. List of involved staff members at University Hospital of Basel
3. Case Report Form (CRF)
4. Patient Information and Informed Consent
  - a. For patients: prospective and retrospective inclusion
  - b. For relatives: prospective and retrospective inclusion

# 1. Introduction

## 1.1. Background and rationale

See study protocol.

## 1.2. Objectives

The objective of this study is to analyse the feasibility and safety of Ultrasound-guided (US-G) Ventriculoperitoneal shunt (VPS) placement. The primary objective of the study is to compare the surgical intervention of VPS placement between US-G and stereotactic navigated placement plus additional 5 minutes.

The Null-hypothesis is that there are no differences in the surgical intervention time (plus additional 5 minutes in the stereotactic navigation group) between the two methods. The Alternative Hypothesis is that US-G VPS placement has a shorter surgical intervention time compared to stereotactic navigated VPS placement.

$$H_0: \text{Time}_{US-G} = \text{Time}_{\text{Stereotactic}} + 5\text{min}$$

$$H_1: \text{Time}_{US-G} < \text{Time}_{\text{Stereotactic}} + 5\text{min}$$

# 2. Study methods

## 2.1. Trial design

This study is a prospective randomized two-arms controlled superiority trial, conducted in a primary neurosurgical centre in Switzerland.

## 2.2. Randomisation

Randomisation will be performed by an independent individual using a stratified simple randomisation procedure as implemented in the electronic data capture software REDCap. An allocation ratio of 1:1 will ensure a balance in sample size across both groups over time. The randomisation will be stratified according to age of the patients (under 40 years/over 40 years).

## 2.3. Sample size

The sample size was estimated with the aim of showing a surgical intervention time reduction of 15 minutes (min) in the intervention arm compared to the control arm. The significance level was chosen to be 5%, while the power was chosen to be  $(1-\beta) = 80\%$ .

Based on unpublished data from a pilot study assessing the surgical intervention time in patients undergoing VPS placement using US navigation, we calculated a mean surgical intervention time of 63 min with a standard deviation (SD) of 28.65 min. Because of the additional steps involved using stereotactically navigated surgery, we assume an increased surgical intervention time in those patients.

We then conservatively selected a scenario with a relatively modest difference between groups. This resulted in 58 patients with VPS placement surgery per group. Anticipating a 1% drop-out by deaths and a surgeons' non-adherence rate (change from control to treatment arm) of 5%, a total sample size of 130 patients (65 per group) was required.

## 2.4. Framework

All endpoints will be analysed for the superiority of US-G VPS placement compared to stereotactic navigated VPS placement.

## 2.5. Stratification

Unless explicitly mentioned, analyses will not be stratified.

## 2.6. Statistical interim analyses and stopping guidance

No interim analysis planned.

# 3. Data management

## 3.1. Data export

The entered data will be exported from the trial database (REDCap) to a statistical software package.

## 3.2. Data validation

Data validation and cleaning will be conducted after completion of data entry but before database lock.

# 4. Statistical principles

## 4.1. General

All recorded and derived variables will be presented by intervention group (and visits, if appropriate) using descriptive summary tables. Continuous variables will be summarised by mean and standard deviation, or median and quartiles. Categorical variables will be summarised with absolute and relative frequencies.

## 4.2. Confidence intervals and p-values

The statistical testing will be two-sided with a significance level of 5%. All tests will be accompanied by an effect measure with a 95% confidence interval (95% CI).

## 4.3. Adherence and protocol deviations

Substantial amendments are changes that affect the safety, health, rights and obligations of participants, changes in the protocol that affect study objective(s) or central research topic, changes of study site(s) or of study leader and sponsor (ClinO, Art. 29).

## 4.4. Analysis populations

The population for analysis will comprise all patients as randomized and with completed follow-up (no drop-outs), hence the full analysis set (FAS). All statistical analyses will be performed on the FAS according to the intention-to-treat principle (i.e. all participants will be analysed on the basis of the intervention to which they were randomly allocated).

The per-protocol (PP) set will include all participants in the FAS who fulfilled the eligibility criteria, for whom the surgery was completed as planned in the study protocol, and for whom the measurement of the primary outcome is available.

## 5. Trial Population

### 5.1. Screening data

Screening data is not collected in the eCRF but the number of screened patients will be calculated from screening logs.

### 5.2. Eligibility

Inclusion and exclusion criteria are defined in the study protocol. Data about reason for non-inclusion is not documented in the eCRF and will not be available.

### 5.3. Patient flow

A CONSORT patient flow diagram will be drawn following the CONSORT 2010 standards.

### 5.4. Withdrawal/loss to follow-up/drop-outs

All withdrawals, drop-outs and losses to follow-up will be listed with time points and reasons (if available).

### 5.5. Baseline patient characteristics

Evaluations of the baseline characteristics will be based on the FAS data set. They will be presented in a descriptive summary table by intervention group. Continuous variables will be shown as mean and standard deviation or median and quartiles, categorical variables as absolute and relative frequencies. No statistical comparisons of patient characteristics at baseline will be performed.

## 6. Analysis

Baseline characteristics:

Preoperative patient data such as age, sex, BMI (body mass index), neurologic examination (GCS, modified Rankin Scale (mRS), Glasgow Outcome Scale (GOS), neurological symptoms (headaches, vomitus, coma, gait disturbances, dementia, urinary incontinence, motor deficit, sensory deficit, aphasia, delir, others), underlying disease causing hydrocephalus, will be collected and summarised for both groups.

### 6.1. Outcomes

Primary outcomes:

- Surgical intervention time («Beginn oper. Vorbereitung (Lagerung)» to «Naht neurochirurgischer Teil») in minutes, plus additional 5 minutes in the stereotactic navigation group

Secondary outcomes:

- Operation time in minutes (time in minutes from “Schnitt” to “Naht”)
- Anaesthesia time in minutes (time in minutes from “Beginn Anästhesie” to “Ende Anästhesie”)
- Number of puncture attempts
- Catheter placement (optimal vs. not optimal, grade I to IV)
- Volumetry of side ventricles pre- and postoperatively in cm^3 (number and relative change)
- Evan’s Index pre- and postoperatively (number and relative change)
- Complications (infection, bleeding, complications ass. with navigation method), mortality
- Revision surgery (yes/no) and reason for revision

Outcome definitions :

The primary endpoint is the surgical intervention time. This is the time spent in the OR by the surgeon and includes the preparation time together (patient positioning, head clamping in the stereotactic navigation group) with the operation time of the neurosurgical part. Beginning (“Lagerung”) and ending (“Naht neurosurgical part”) of this time interval is clearly defined and will be in a standardized manner recorded by blinded anaesthesiologists. In the stereotactic navigation group, an additional 5 minutes will be added to the surgical intervention time for the preplanning of the navigation the day before the operation on the Brainlab workstation.

The optimal catheter placement has been defined as free-floating within the CSF without touching the ventricle wall or septum pellucidum, and the tip of the catheter located at the foramen of Monro showing an optimal length of the catheter. Catheters that did not fulfill all criteria have been defined as not optimally placed. Positioning of catheters will be further graded according to Yim et al. into grades I to IV (grade I: catheter terminates in the ipsilateral frontal horn, grade II: catheter terminates in contralateral frontal horn, grade III: catheter terminates in non-targeted CSF spaces, grade IV: catheter terminates intraparenchymally).

### 6.3. Analysis methods

#### 6.3.1 Primary analysis

Analysis of the primary endpoint will follow the intention-to-treat (ITT) principle. It will be based on the FAS with missing data of the primary outcome imputed as described in the section “Missing data” (section 6.4). Patient data will be analysed according to their intervention allocation, irrespective of actual treatment received.

The primary outcome, surgical intervention time, will be assessed using a linear regression model. The estimates will be reported with 95% confidence intervals (CI). Explanatory variables will be BMI, underlying diagnosis, experience surgeon and the use of an old burr hole.

In case the outcome variable is not normally distributed, data will be transformed or a different model, depending on the distribution of the data, chosen.

##### 6.3.1.2. Analysis of secondary outcomes

All analysis of the secondary endpoints will follow the intention-to-treat (ITT) principle. It will be based on the FAS with missing data of the primary outcome imputed as described in the section “Missing data” (section 6.4).

The continuous secondary endpoints (outcomes operation time, anaesthesia time, volumetry of side ventricles, and Evan’s Index) will be assessed using linear regression models, the binary endpoints (optimal catheter placement, complications, mortality and revision surgery) will be assessed using logistic regression, and the number of puncture attempts will be assessed using a poisson regression model.

All estimates will be reported with 95% CI. IF numbers allow explanatory variables will be BMI, underlying diagnosis, experience surgeon and the use of an old burr hole.

In case the outcome variable is not normally distributed or model assumptions are violated, data will be transformed or a different model, depending on the distribution of the data, chosen.

Deviation from the original statistical plan:

If substantial deviations of the analysis as outlined in these sections are needed for whatever reason, the protocol will be amended. All deviations of the analysis from the protocol or from the detailed analysis plan will be listed and justified in a separate section of the final statistical report.

#### 6.4. Missing data

Missing baseline and outcome data will be summarized by study arm. As outlined above, the primary analyses will be the intent-to-treat population. In the case of missing data or drop-outs, we may adjust for further baseline variables which are associated with missing outcome data or we consider multiple imputation. Both, baseline patient characteristics and outcome variables will be considered for multiple imputations. Variables with more than 50% missing values will not be used for the imputation model. Categorical variables with a frequency of 5% or less in one category will also be omitted. Continuous variables will be imputed using linear regression and binary variables using logistic regression. We will construct and analyze 20 imputed data sets and combine results using Rubin's rules. Diagnostic checks, including model convergence and comparing observed versus imputed distributions, will be performed to ensure the quality of imputations.

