## 9.3 Procedures at each visit

### 9.3.1 Visit 1: Screening and admission

Randomisation, demographics (age, gender), height, weight, body mass index (BMI), neurologic examination (GCS, modified Rankin Scale (mRS), Glasgow Outcome Scale (GOS), neurological symptoms (headaches, vomitus, coma, gait disturbances, dementia, urinary incontinence, motor deficit, sensory deficit, aphasia, delir, others), medical history (underlying disease causing hydrocephalus (NPH, SAH, IVH, other type of bleeding, trauma, tumor, congenital, other), prior EVD, prior VPS, or prior head operations including details), cCT scan (US group not older than 90 days, stereotactic navigation group not older than 5 days, measurements: Evans' index, volumetry of side ventricles). Randomisation and cCT scan (indications see above) is the only measurements done for the study, all the other measurements are generally assessed for all patients receiving this operation.

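### SAP 6.4 imputes ventricular volumes by unbounded linear regression, so a missing preoperative volume can become a near-zero or negative divisor and inflate the standard error of relative change

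*Combined protocol and SAP*

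**What the plan says.** SAP 6.4 allows two responses to missing data. The first is adjustment: "In the case of missing data or drop-outs, we may adjust for further baseline variables which are associated with missing outcome data". The alternative is multiple imputation with 20 data sets combined by Rubin's rules. On scope it says: "Both, baseline patient characteristics and outcome variables will be considered for multiple imputations". On method it says: "Continuous variables will be imputed using linear regression and binary variables using logistic regression". It adds an exclusion: "Categorical variables with a frequency of 5% or less in one category will also be omitted". Observed and imputed distributions are to be compared, but no action is stated if they disagree.

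SAP 6.1 lists "Volumetry of side ventricles pre- and postoperatively" in cm³, as a value and as relative change. SAP 6.3.1.2 analyses volumetry by linear regression, together with operation time, anaesthesia time and the Evans index. It treats punctures separately: "the number of puncture attempts will be assessed using a poisson regression model". For the primary model, SAP 6.3.1 states: "Explanatory variables will be BMI, underlying diagnosis, experience surgeon and the use of an old burr hole". Protocol 9.3.1 records the diagnosis in eight groups: "underlying disease causing hydrocephalus (NPH, SAH, IVH, other type of bleeding, trauma, tumor, congenital, other".

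**The concern.** A volume is strictly positive and probably right-skewed. A linear-regression draw is normal around its prediction, so it can land close to zero or below it. For the raw volume such a draw is only implausible. For relative change it can be far worse, because the preoperative value is presumably the divisor: a draw near zero gives an enormous ratio and a negative draw reverses its sign. The excess variability goes straight into the within- and between-imputation variances that Rubin's rules combine. A step meant to keep patients in the analysis can then cost more precision than it saves. A missing postoperative volume does not have this effect, because it enters only the numerator.

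**Working it through.** **1. The plan's own figures.** The documents give no mean, SD or missing rate for volumes, so there is no stated figure to reproduce on this point. The sample size does reproduce: 2 × (1.960 + 0.842)² × 28.65² / 15² = 57.3, so 58 per group; 58 / (0.99 × 0.95²) = 64.9, so 65 per group. It concerns surgical intervention time and is untouched here. The protocol's enlarged total of 136 (68 per group) is used below.

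**2. How often a draw is inadmissible.** Ignoring covariates, P(draw < 0) = Φ(−mean/SD). Assumed volumes in cm³:
- mean 120, SD 30: Φ(−4.0), about 0%
- mean 120, SD 50: Φ(−2.4) = 0.8%
- mean 100, SD 60: Φ(−1.67) = 4.8%
- mean 60, SD 40: Φ(−1.5) = 6.7%

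Conditioning on postoperative volume lowers these; in simulation about 3% of draws remained negative at a CV of 60%. With 10% missing in one arm (0.10 × 68, about 7 patients) and 20 imputations there are 140 draws, so about 4 would be negative.

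**3. What one such draw does.** Take a postoperative volume of 100 and an imputed preoperative value of 5: relative change is (100 − 5)/5 = 19, or +1900%.

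**4. Effect on the comparison.** Simulation, 200 runs per scenario: 68 per arm, log-normal volumes with mean 110 cm³, 20 imputations, Rubin's rules, missing preoperative volumes in one arm only. Median 95% CI width for the difference in mean relative change:

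| CV | Missing | Log-scale correlation | Complete | Linear | Matching | Linear ÷ complete | Matching ÷ complete |
|---|---|---|---|---|---|---|---|
| 40% | 5% | 0.70 | 0.185 | 0.203 | 0.188 | 1.10 | 1.02 |
| 40% | 5% | 0.85 | 0.124 | 0.132 | 0.126 | 1.06 | 1.02 |
| 40% | 10% | 0.70 | 0.183 | 0.225 | 0.189 | 1.23 | 1.03 |
| 40% | 10% | 0.85 | 0.125 | 0.139 | 0.128 | 1.11 | 1.02 |
| 60% | 5% | 0.70 | 0.280 | 0.437 | 0.284 | 1.56 | 1.01 |
| 60% | 5% | 0.85 | 0.188 | 0.284 | 0.189 | 1.51 | 1.01 |
| 60% | 10% | 0.70 | 0.281 | 0.617 | 0.289 | 2.20 | 1.03 |
| 60% | 10% | 0.85 | 0.187 | 0.397 | 0.194 | 2.12 | 1.04 |

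A separate simulation compared standard errors (correlation 0.70, postoperative volume in the imputation model). The median ratios to complete data were 1.05-1.17 at CV 40% and 1.41-2.84 at CV 60%, against 1.01-1.03 for matching. With one missing value the linear medians were 1.01-1.03, but a tenth of runs exceeded 1.23 to 2.64, depending on the scenario.

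**5. Postoperative volume in the imputation model.** In a further simulation with CV 50%, 5% missing and a complete-data standard error of about 3.0 percentage points, the median standard errors were:
- postoperative volume included: linear 3.6, matching 3.1
- postoperative volume left out: linear 22.8, matching 4.8

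So matching alone is not enough; both volumes must be in the imputation model.

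**6. Count and diagnosis.** No imputation model is named for either. Under the 5% rule a diagnosis group of six or fewer is enough to omit the variable (0.05 × 136 = 6.8). The chance that at least one of eight groups is that small is 1% with equal shares, and 47% or 91% for two assumed uneven mixes. Diagnosis would still be a covariate of the primary model, with no stated handling of its missing values.

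**The case against.** The strongest reply is that the trigger may never occur. Multiple imputation is one of two options in SAP 6.4 and only a possible sensitivity analysis in protocol 11.5. SAP 6.3.1.2 names only the primary outcome as imputed for the secondary analyses, which does not match the wider scope in 6.4. Preoperative imaging is required in both arms, punctures are recorded on the operation day, and SAP 4.4 removes drop-outs from the full analysis set. Missing values should therefore be few. All of this stands and keeps the point minor. It does not remove it: protocol 8.2.1 accepts a CT or MR scan in the ultrasound arm while 9.2.2 measures volumes on CT, so some one-sided missingness is conceivable, at an unknown rate.

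The check of imputed against observed distributions could expose negative volumes. However, no remedy is stated, so the replacement method would be chosen after seeing the data. The fallback to a transformation or another model in 6.3.1 and 6.3.1.2 concerns the analysis model.

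The divisor problem also disappears if relative change itself is imputed. The SAP does not say which quantity is imputed.

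Some stronger readings are tempting and should not be drawn:
- **Every non-binary variable is imputed linearly.** The text says continuous variables, and 6.3.1.2 handles punctures separately as a count. Negative or fractional puncture draws would follow from a rule that the SAP does not state.
- **Catheter grade needs an imputation model.** No analysis model uses grade; only optimal versus not optimal is modelled.
- **The puncture analysis would fail.** R does stop on a negative Poisson count, but the error would be visible and corrected.
- **The results would be biased.** The simulations show lost precision; no bias was demonstrated.

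**Conclusion.** The point holds for ventricular volumes. As written, the continuous-variable rule gives unbounded draws for a positive quantity that is probably also a divisor. With 5-10% of preoperative volumes missing in one arm, the median standard error of the relative-change comparison rises to about 1.05-1.2 times its complete-data value at CV 40% and 1.4-2.8 times at 60%, against about 1.00-1.03 with predictive mean matching. With one missing value the median effect is negligible and the risk lies in the tail.

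This rests on assumed log-normal volumes, assumed spread, correlation and missing rates, division by the baseline value, and the optional imputation being used. The silence on the puncture count and on diagnosis is mostly missing detail; diagnosis matters more because it enters the primary model. This is a minor point, worth making because a better method costs almost nothing.

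**What to change.** In SAP 6.4:

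1. Replace linear regression by predictive mean matching for continuous variables, or impute volumes and times on the log scale.
2. Put treatment arm and both the pre- and postoperative values in the imputation model.
3. Calculate relative change after imputation, and state its divisor.
4. For completeness, use matching for the puncture count and a multinomial model for underlying diagnosis. Exempt diagnosis from the 5% omission rule, or merge its sparse categories without regard to arm.
5. State what is done if a diagnostic check fails, and align the imputation scope in 6.3.1.2 with 6.4.

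The cost is SAP wording only. The methods are available in R, the planned software, and no new data or change in sample size is needed. The downside is negligible; sparse diagnosis groups may have to be merged for the multinomial model to be stable.
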